## Abstract

**Background:**

Life trauma is highly prevalent in the general population and posttraumatic stress disorder is among the most prevalent psychiatric consequences of trauma exposure. Brazil has a unique environment to conduct translational research about psychological trauma and posttraumatic stress disorder, since urban violence became a Brazilian phenomenon, being particularly related to the rapid population growth of its cities. This research involves three case-control studies: a neuropsychological, a structural neuroimaging and a molecular neuroimaging study, each focusing on different objectives but providing complementary information. First, it aims to examine cognitive functioning of PTSD subjects and its relationships with symptomatology. The second objective is to evaluate neurostructural integrity of orbitofrontal cortex and hippocampus in PTSD subjects. The third aim is to evaluate if patients with PTSD have decreased dopamine transporter density in the basal ganglia as compared to resilient controls subjects. This paper shows the research rationale and design for these three case-control studies.

**Methods and design:**

Cases and controls will be identified through an epidemiologic survey conducted in the city of São Paulo. Subjects exposed to traumatic life experiences resulting in posttraumatic stress disorder (cases) will be compared to resilient victims of traumatic life experiences without PTSD (controls) aiming to identify biological variables that might protect or predispose to PTSD. In the neuropsychological case-control study, 100 patients with PTSD, will be compared with 100 victims of trauma without posttraumatic stress disorder, age- and sex-matched controls. Similarly, 50 cases and 50 controls will be enrolled for the structural study and 25 cases and 25 controls in the functional neuroimaging study. All individuals from the three studies will complete psychometrics and a structured clinical interview (the Structured Clinical Interview for DSM-IV and the Clinician-Administered PTSD Scale, Beck Anxiety Inventory, Beck Depression Inventory, Global Assessment of Function, The Social Adjustment Scale, Medical Outcomes Study 36-Item Short-Form Health Survey, Early Trauma Inventory, Clinical global Impressions, and Peritraumatic Dissociative Experiences Questionnaire). A broad neuropsychological battery will be administered for all participants of the neuropsychological study. Magnetic resonance scans will be performed to acquire structural neuroimaging data. Single photon emission computerized tomography with [(99m)Tc]-TRODAT-1 brain scans will be performed to evaluate dopamine transporters.

**Discussion:**

This study protocol will be informative for researchers and clinicians interested in considering, designing and/or conducting translational research in the field of trauma and posttraumatic stress disorder.

## Background

Posttraumatic stress disorder (PTSD) occurs following exposure to a potentially traumatic life event and is defined by three symptom clusters: reexperiencing, avoidance and numbing, and arousal [1]. However, PTSD is relatively rare event in trauma-exposed people. This fact has motivated research aimed at identifying risk factors for this disorder. Two meta-analyses of PTSD risk factors have come to some consensus as to the key factors influencing PTSD vulnerability. These include small but consistent effects on risk for pre-trauma factors such as cognitive ability, family psychiatric history, pre-trauma psychological adjustment, child abuse, other previous trauma exposures, and general childhood adversity [2,3]. Characteristics of the traumatic experience were found to be particularly important, especially trauma severity, perceived life threat and peri-traumatic emotional reactions such as dissociation [2,3]. A dose-response relation between severity of exposure and conditional risk of developing PTSD has been well-documented [4,5]. Post-trauma social support also appears to play a role [2,3]. However, the risk factors models supported by meta-analytic studies explain only about 20% of the variance in PTSD; clearly new variables need to be incorporated into models of PTSD vulnerability. Due in part to methodological limitations of extant research, the role of neuropsychological and brain structure and functional factors in the etiology of PTSD are less well understood.

This paper describes the protocol for the Project Post-Traumatic Stress Disorder in Brazil which is aimed at characterizing the underlying biology of PTSD neuropsychological assessment, neurostructural evaluation and molecular imaging of the dopamine transporter system. Brazil offers a unique environment to conduct translational research about psychological trauma and PTSD. From 1980 to 2000, a total of more than 598 thousand people died in Brazil because of homicide with two thirds of this occurring in the 90's. In 1980 the leading cause of violent death in the country was traffic accidents but in 2000 it was homicides [6,7]. From 1991 to 2000 there was an increase of 27% in the proportion of deaths caused by homicides among the total deaths in the country. Thus, lethal violence became a national phenomenon, being particularly related to the rapid population growth of large and urban cities [8].

### Neuropsychological findings in PTSD

PTSD is characterized by re-experiencing of the traumatic event and the inability to consciously recall facts about the traumatic event as well as by altered emotional processing of trauma-relevant cues. The patient's memory seems to be fixed on the traumatic event, and the retrieval of others memories seems to be inhibited [9-11]. Previous research on the neuropsychology of PTSD has identified several neurocognitive deficits [12]. Neuropsychological measures of intellectual ability, learning, memory (verbal and non-verbal), attention, visuospatial ability, executive functioning, language, psychomotor speed have been examined. Several studies have identified impaired performance on verbal memory and learning in PTSD cases as compared to controls [13-16]. Other studies have documented differences between cases and controls in different domains, including attention, working memory [17-22], and processing speed [21]. Although there is evidence for memory impairment in PTSD subjects, it remains unclear whether memory impairment is confined to verbal material or nonverbal material is also affected [11,14,21]. Different studies, have found impaired visual memory in individuals with PTSD [18,19,23,24].

Many studies have shown impairments in the whole mnemonic process (immediate memory, recall and recovery), attention, learning, intellectual level, and emotional processing [25]. Nonetheless, others studies have shown no differences between cases and controls for memory [24,26-29] and/or attention performance [12,13,30]. Those neuropsychological findings suggest involvement of two primary strcutures: hippocampus and prefrontal cortex. Several studies have reported decreases in hippocampal volume [31-36] and hippocampal N-acetylaspartate [37-39] as well as an association between hippocampal atrophy and poor verbal memory in PTSD subjects [23]. Neurofunctional studies have indicated specific findings in limbic regions, although the relationship of these results to neuropsychological performance remains to be explored [40].

An alternative model of PTSD may be related to a dysfunction of higher-level attentional resource which in turn might affect activity in other systems concerned with memory and thought [20,41,42]. Attention and concentration difficulties appear to be core deficits in PTSD and memory deficits might actually be secondary to an impaired attention. A possible explanation for the association between memory and attention difficulties in PTSD is that explicit memory performance may be impacted by impaired attention resources during processing. Some researchers have theorized that the heightened emotional reactivity in patients with PTSD disrupts attentional resources [43]. Impaired attention prevents sufficient registration of information, which in turn prevents consolidation and retrieval of memory. Furthermore, recent studies have demonstrated a possible deficit in the inhibitory processes of memory in PTSD [18,19,44].

Several potential confounding factors must be considered for neuropsychological evaluation of PTSD patients including comorbid depression, substance abuse, and medical conditions, type of trauma, and motivational aspects. Therefore, any conclusion if deficits observed are specifically related to PTSD should take into account alternative explanations such as the possible effect of confounding factors [26,40]. In conclusion, neuropsychological functioning has emerged as promising endophenotype to be explored in PTSD.

### Neurostructural findings in PTSD

One of the possible mechanisms underlying the physiopathology of PTSD is the damaging action of glucocorticoids on hippocampus [45]. The hippocampus plays a central role in neuropsychological functions such as memory and emotional behaviour and is likely to be involved in the development of PTSD. An alternative model would be a failure in the regulatory activity of prefrontal cortex over amygdala, with a consequent hyperactivity of the later in response to traumatic memories [46-48]. This inhibitory deficiency is also a possible explanation for the hyperexcitability symptoms found in PTSD. The orbitofrontal cortex, the ventral portion of prefrontal cortex, appears to be central in the regulation of prefrontal cortex over amygdala and is also implicated in the processing of negative emotion [49]. Studies using different techniques have consistently found neurofunctional abnormalities in this region in PTSD patients [50-52]. Furthermore, some symptoms that may be seen in PTSD, such as poor impulse control and violent assaults, are also reported in individuals with lesions in orbitofrontal cortex [53,54]. Findings from magnetic resonance imaging studies have suggested neurostructural alterations in PTSD. Although these findings are less consistent than those seen in neurofunctional studies, volumetric reductions in hippocampus [23,32,34-36,51,52] and prefrontal regions [55,56] have been reliably found. However, additional studies are still warranted in order to assess whether these structural abnormalities are specific to PTSD or represent non-specific morphological abnormalities associated to trauma exposure. Further examination of abnormalities in frontolimbic structures are also required to clarify the role of structural and functional brain abnormalities in the pathophysiology of PTSD.

### Molecular imaging of dopamine transporter in PTSD

Physiological response to stressful experience involves a vast neural-endocrine-immunologic reaction that leads to the release of catecholamines and autonomic nervous system stimulation [57]. Noradrenergic and hypothalamus-pituitary-adrenal axis systems are the most common studied in response to stress [58] but many other neural-chemical systems are implicated. In animal studies, dopaminergic innervation of the basolateral nucleus of the amygdala, the medial prefrontal cortex and other limbic regions is highly responsive to stress and may be altered by stress [59-61]. Also the enhancement of the acoustic startle response, which can be a symptom of PTSD, has been related to the dopamine D1 receptor agonists in rats [62]. Genetically determined alterations in dopamine release and dopamine receptor expression in mice have been implicated in behavioral abnormalities induced by chronic stress [63]. This finding was interpreted as suggesting that stress-induced alterations of central dopaminergic neurotransmission may be genotype-dependent and expressed in behaviour. Human studies showed that there was a relationship between urinary excretion of dopamine and plasma dopamine and (the severity of) PTSD symptoms [64].

Evidence from genetic studies has proposed that reduced density of D2 dopaminergic receptor predisposes to PTSD [65]. There are two important PTSD candidate genes that directly affect the dopamine system: the dopamine receptor gene (DRD2) and the dopamine transporter (DAT) gene. The D2 dopamine receptor (DRD2) minor (A1) allele DRD2 A1 has already been linked to ADHD, Tourette's syndrome, conduct disorder and substance abuse [66]. This prompted suppositions that this gene may be involved in stress response in humans [61]. Polymorphism of the dopamine transporter (DAT) gene, in the locus SLC6A3 3' (VNTR), has been found to predispose to PTSD and to chronic forms of the disorder [67]. Taken together, these evidences suggest a relevant role for dopamine in the pathogenesis of PTSD.

To gain more clarity about any link between PTSD and the DAT, it is therefore important to clearly document PTSD patients, controlling confounders as alcohol consumption, major depression and clinical illness, through a functional neuroimaging investigation.

Although molecular imaging allows reliable information on in vivo dopaminergic function [68], no studies, to our knowledge, has examined dopaminergic system activity in PTSD patients using molecular neuroimaging techniques.

The main reasons that justify such an effort to understand the problem of violence and its consequences for mental health can be described as follows: 1) Treatment strategies to be sponsored by the Brazilian public health care system need to be based on solid local data on the extent and nature of the disorder; 2) Exposure to traumatic life events is related to not only with mental disorders which include PTSD and depression, but also with other cognitive and neurotransmission dysfunctions [18,19,44,69]. The impact in mental health of the population of exposure to violence among the population of Sao Paulo, a large urban centre in a Middle Income Country (MIC), as well as specific parameters such as neurocognitive, neurostructural anf functional neuroimaging finds is virtually unknown.

The subjects of the study will be selected from an epidemiological/genetic survey in the city of Sao Paulo to assess the relationship between exposure to violence and the prevalence of PTSD and common mental disorders. Subjects located in the epidemiological/genetic survey will be referred to these three case-control studies, reported here, and to a randomized controlled clinical trial on the efficacy of topiramate for the treatment of PTSD symptoms.

This protocol is the result of collaborative task force to conduct translational research in the field of traumatic stress in urban regions of Brazil. The current project investigates possible causes for neurocognitive deficits, neurostructural changes and dopaminergic dysfunction in individuals with PTSD. We will be comparing individuals with current or lifetime diagnosis of PTSD with those who were exposed to a traumatic event but did not develop a current or a lifetime diagnosis of PTSD.

The main objectives of this project are:

1. to examine cognitive functioning of PTSD subjects and its relationships with symptomatology;

2. to evaluate neurostructural integrity of orbitofrontal cortex and hippocampus in PTSD subjects;

3. to evaluate if patients with PTSD have decreased dopamine transporter density in the basal ganglia as compared to resilient controls subjects.

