## Methods and design

### Sample

Cases and controls will be identified through an epidemiologic survey conducted in the city of São Paulo. Details of the epidemiologic study are presented in a companion paper (cite) and are summarized here. To identify trauma victims in the community, interviews were conducted by a professional team specialized in household surveys, the Brazilian Institute of Public Opinion and Statistics. Interviewers were trained at the CIDI [70] in the Federal University of São Paulo, an accredited center by the World Health Organization (WHO). Training procedures were conducted in accordance to the guidelines set up by the WHO. Interviews were carried out in the participants households by means of printed questionnaires. All questionnaires were translated into Portuguese and adapted to the local social and cultural context. Inclusion and exclusion criteria for the three case-control studies are described in tables 1 and 2, respectively. Individuals who met inclusion criteria during the epidemiologic study were invited to participate in the case-control study. Subjects exposed to traumatic life experiences resulting in PTSD (cases) will be compared to resilient subjects victims of traumatic life experiences without PTSD (controls) aiming to identify biological variables that might protect or predispose to PTSD. This case-control design will enrol representative subjects from the community being this procedure an important technique to overcome Berkson bias. Subjects will be informed about the procedures of the studies and will be asked to formally consent willingness to participate. Subjects who consent to participate in the case-control studies will receive the following assessment:

**Table 1 T1:** Inclusion criteria for PTSD cases (p) and control (c) groups

	Neuropsychological Study		Structural Neuroimaging study		Molecular Neuroimaging study	
	p	C	P	c	p	c
Age between 18 and 60 (inclusive)	X	X	X	X	X	X
Life time history of traumatic life experience as defined in criteria A of DSM IV criteria for PTSD	X	X	X	X	X	X
PTSD diagnosis according DSM IV criteria as assessed by SCID I applied by trained psychiatrists or psychologists	X		X		X	
Good general health with no additional diseases expected to interfere with the study	X	X	X	X	X	X
Able to understand and signed informed consent	X	X	X	X	X	X
Completed 5 years grades of education	X	X				
						
Fluent in Portuguese	X	X	X	X	X	X
Willing and able to complete all assessments	X	X	X	X	X	X

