#### Data management and Analyses

1) Questionnaires will be double typed and data will be entered on SPSS software data files. Participants will be divided into two categories, according to the diagnosis: (1) lifetime diagnosis of PTSD and (2) Traumatic experience, but no lifetime diagnosis of PTSD. The following comparisons will be carried out in the two groups:

1) Neuropsychological Study: neuropsychological measures of PTSD cases compared to controls;

2) Magnetic resonance imaging study: to assess neurostructural abnormalities in OFC and hippocampus of patients with PTSD compared to resilient controls;

3) Molecular neuroimaging study: dopamine transporter density using single photon emission tomography of PTSD cases compared to controls.

Data will be codified and analyzed using the Statistical Package for Social Sciences (SPSS for Windows, version 15.0). Proportion differences will be compared using the Chi Square test or Fisher's exact test, as appropriate. Continuous variables will be compared by Analysis of Variance (ANOVA) or Mann-Whitney test for non-parametric data. All significant tests will be considered as 2-tailed. P values < 0.05 will be considered statistically significant. Because of the exploratory nature of the study, we do not consider alpha adjustment in multiple comparisons and we did not calculate the sample size (Table 3). The main analyses will examine the relationship between exposure to traumatic events and the PTSD occurrence. Unadjusted relative risk for studied variables cognition, cortisol level, hippocampal volume, and dopamine transporter density (and 95% confidence intervals) are presented for trauma without PTSD and trauma with PTSD, both with and without adjustment for age (18–29 years, 30–39 years, 40–49 years, 50–60) and gender. As a secondary analysis, we will be adjusting for clinical and demographic variables previously associated with PTSD: marital status, country of birth, socio-economic status, urbanicity and employment status.

**Table 3 T3:** Sample size in each study for PTSD cases and control groups

	Neuropsychological study		Structural Neuroimaging study		Molecular Neuroimaging study	
	
	Case	Control	Case	Control	Case	Control
Number of individuals for each group	100	100	60	60	25	25

PTSD = Posttraumatic stress disorder; MRI = Magnetic Resonance Imaging

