Despite the unquestionable progress in identification of neurocognitve and neuroanatomical abnormalities associated with PTSD over the past decade or so, it remains unclear whether neurostructural and neuropsychological alterations are specific to PTSD or are related to unspecific environmental factors such as stress and substance abuse. The findings from this neuropsychological study, together with data from neurostructural investigation, may offer an uncommon opportunity to examine the convergence of cognitive and neuroanatomical alterations in patients with PTSD. Stress-induced functional and structural alterations in hippocampus and OFC may mediate many of the symptoms of PTSD that are related to memory dysregulation and hyperexcitability. Interestingly, reversion of both neuropsychological and neuroanatomical abnormalities has been demonstrated after treatment with paroxetine, which in turn has been shown to promote neurogenesis in animal studies [97]. The increasing use of sophisticated neuroimaging techniques is certainly enhancing our understanding of PTSD, potentially improving prevention, treatment, and cognitive rehabilitation programs [23].

Although a previous study showed involvement of DAT gene in PTSD [67], and other indirect investigations have suggested a connection between dopaminergic system and stress [61], insufficient research has been done on the role of the DAT in relation to PTSD. To the best of our knowledge this will be the first SPECT study investigating dopamine transporter density in patients with PTSD and well matched resilient controls coming from an epidemiologic sample. The results of this study will help to disentangle whether possible dopaminergic changes in PTSD are a "state condition" or a "trait" marker of this disorder, raising a discussion why some subjects exposed to trauma develop PTSD and some others do not. Moreover, further studies evaluating patients with PTSD, resilient controls and healthy control subjects (who never experienced trauma) would provide useful information to clarify whether dopaminergic abnormalities are related to PTSD itself or to psychological trauma exposure.

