Advances in molecular imaging techniques, such as SPECT, have made important contributions to the understanding of the pathophysiology of neuropsychiatric disorders [98]. Molecular imaging approaches are more sensitive than Neuroanatomical imaging techniques, and are able to identify subtle cerebral pathophysiological changes before neurostructural abnormalities take place. One of the major goals of molecular imaging research has been the identification of biomarkers, which are defined as the characteristics that are objectively measured and can differentiate normal biologic processes from pathogenic processes. These approaches has the potential to provide accurate and early neuropsychiatric recognition, evaluate disease progression, and monitor treatment efficacy [68].

These studies have several important limitations. First, cases are recruited after they have developed PTSD. Assuming we find differences between cases and controls on neuropsychological/imaging variables, we will not be able to determine whether these differences reflect a risk factor or a consequence of the disorder. Second, in several situations both cases and controls, were exposed to traumatic experience years before the investigations, producing a potential recall bias.

This study protocol intends to be helpful for researchers and clinicians interested in designing and/or conducting translational research in the field of trauma and posttraumatic stress disorder.

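### One pooled lifetime-PTSD case group gives a single cross-sectional difference, which cannot separate a state from a trait marker as the Discussion suggests the SPECT study will help to do

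*Protocol article*

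**What the plan says.** The Background (end of the section on molecular imaging of the dopamine transporter) defines the comparison: "We will be comparing individuals with current or lifetime diagnosis of PTSD with those who were exposed to a traumatic event", the controls being exposed people with neither a current nor a lifetime diagnosis. Data management and Analyses fixes the groups as ("1) lifetime diagnosis of PTSD and (2) Traumatic experience, but no lifetime diagnosis of PTSD") and then states: "The following comparisons will be carried out in the two groups". All three comparisons listed there, one per study, are cases against controls.

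Table 1 asks of cases a "PTSD diagnosis according DSM IV criteria as assessed by SCID I applied by trained psychiatrists or psychologists". It does not require the diagnosis to be current. The Measures section lists the CAPS as covering both current and lifetime PTSD, so current status is recorded.

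On the SPECT study the Discussion says: "The results of this study will help to disentangle whether possible dopaminergic changes in PTSD are a" state condition or a trait marker. The limitations paragraph that follows concedes, for all three studies, that "we will not be able to determine whether these differences reflect a risk factor or a consequence of the disorder".

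**The concern.** A state marker is abnormal while a person is ill and returns towards normal on remission. A trait marker is abnormal whether or not the person is ill now. Telling them apart needs information on people with past but not current illness, or repeated measurement of the same people. The stated plan puts current and remitted cases into one mean and compares it once with controls, so the distinction is averaged away before the analysis starts.

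Two things are at stake. The first is interpretation: a SPECT difference could be presented as bearing on state versus trait when the analysis does not address it. The second is sensitivity. If the abnormality belongs to current illness, remitted cases pull the case mean towards the control mean, and this matters most in the smallest study (25 versus 25). The article makes a state effect plausible: the Background cites a relation between dopamine levels and PTSD symptom severity, and the Discussion cites reversal of neuropsychological and neuroanatomical abnormalities after treatment.

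**Working it through.** **Inputs from the article.** Two-sided tests at 0.05. Group sizes are 25 (SPECT), 100 (neuropsychology), and 50 in the Abstract or 60 in Table 3 (structural MRI); both MRI figures are carried. No effect size, SD or power is stated, so there is no planned figure to reproduce.

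**Assumptions, not from the article.** Standardised effect d = 0.5 in current PTSD; remitted share f of 20%, 30% or 50%.

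**1. What the planned contrast estimates.** Let d_c and d_r be the effects in current and remitted cases. The pooled difference is

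d_pooled = (1 − f)·d_c + f·d_r.

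This is one equation in two unknowns. With f = 0.5, a pooled difference of 0.25 arises from d_c = 0.5 and d_r = 0 (pure state) and equally from d_c = d_r = 0.25 (pure trait). The planned comparison cannot tell these apart at any sample size. This step needs no assumption about the true effect.

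**2. Dilution if the effect is confined to current illness (d_r = 0).** Then d_pooled = 0.5(1 − f), which is 0.40, 0.35 and 0.25. Power of the two-sample t-test:

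| Per group | f = 0 | 20% | 30% | 50% |
|---|---|---|---|---|
| 25 | 41% | 28% | 23% | 14% |
| 50 | 70% | 51% | 41% | 24% |
| 60 | 78% | 58% | 48% | 27% |
| 100 | 94% | 80% | 69% | 42% |

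Allowing for the extra variance from mixing two kinds of case changes these figures by about one percentage point at most.

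**3. No dilution if remitted cases are equally abnormal (d_r = d_c).** Then d_pooled = d_c whatever f is, and the f = 0 column applies throughout.

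**4. What restricting cases to current PTSD would do (SPECT, d = 0.5).** With 25(1 − f) current cases against 25 controls, power is 37%, 35% and 29% for f = 20%, 30% and 50%. Under the state model this beats the pooled 28%, 23% and 14%. Under the trait model it is a loss from 41%.

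**5. The contrast that does bear on state versus trait (SPECT).** With 25f remitted and 25(1 − f) current cases, the standard error in SD units is √(1/(25f) + 1/(25(1 − f))):

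- f = 20% (5 versus 20): √(0.20 + 0.05) = 0.50
- f = 50% (12.5 versus 12.5): √(0.08 + 0.08) = 0.40

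The difference detectable with 80% power is (1.960 + 0.842) × SE, that is 2.802 × 0.50 = 1.40 and 2.802 × 0.40 = 1.12. For d = 0.5, t-test power is 16%, 20% and 22% at f = 20%, 30% and 50%. The 95% confidence interval has a half-width of 2.069 × 0.50 = 1.03 SD at f = 20% and 2.069 × 0.40 = 0.83 SD at f = 50%.

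**The case against.** The strongest defence is that lifetime versus never is the right contrast for the main question. The Sample section says that the studies look for biological variables that may protect against PTSD or predispose to it. For that question a person who had PTSD and recovered is a true case, and a never-PTSD control group is the matching comparator. Restricting cases to current illness would mix predisposition with persistence. This stands, and it settles the choice of main contrast.

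A reader might infer that the pooling simply dilutes the result. The documents do not support that: dilution depends on remitted cases being less abnormal and on a remitted share that is not given. A reader might also infer that current versus never should become the main contrast. That gains power under one model and loses it under the other. Moreover, separate tests of current and remitted cases against controls do not show that current and remitted differ, even when one is significant and the other is not.

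The Discussion wording is also softer than a promise: it speaks of helping, it concerns SPECT only, and state versus trait is not among the three numbered objectives. Nor is it in strict contradiction with the limitations paragraph, since risk factor versus consequence concerns order in time and state versus trait concerns persistence. Both points are fair, but neither rescues the sentence, because the stated comparison gives no help on the question.

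Finally, detailed symptom models may sit in a fuller protocol that is not shown, so their absence here is not itself a fault. The point rests on what the article does fix: two groups, and comparisons between them.

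**Conclusion.** The point holds in a limited form. The state-versus-trait statement claims more than the stated analysis can deliver, and this conclusion rests on no numerical assumption. The loss of power is conditional. At 25 per group it ranges from none (remitted cases equally abnormal) to a fall from 41% to 14% (d = 0.5, no effect in remitted cases, half of cases remitted). Where the studies fall in that range cannot be said from the documents. The lifetime-versus-never main contrast is not an error. Even with current and remitted cases separated, 25 SPECT cases could give only a rough answer, so in that study the essential change is to the wording.

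**What to change.** 1. Keep lifetime PTSD versus never PTSD as the main contrast in all three studies, and state that it addresses predisposition.
2. Using the SCID/CAPS current status at assessment, prespecify as secondary analyses: (a) current and remitted cases reported separately beside controls; (b) a direct current-versus-remitted difference with its 95% confidence interval; (c) within cases, a regression of each measure on current CAPS score, which also serves the symptomatology part of objective 1.
3. Report the number of current and remitted cases in each study, so that readers can judge possible dilution.
4. Reword the Discussion sentence on state versus trait to claim association only, in line with the limitations paragraph.

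No new data are needed. The cost is a few extra secondary analyses and one changed sentence. The SPECT secondary results will be imprecise and should be read as estimates, not as tests.
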